### Data collection management and security {11c, 19}

All patient-reported outcome data will be simultaneously collected and entered using REDCap [76, 77]. Data collected by other electronic means (computerized dynamometry, accelerometer, bioelectrical impedance) will be converted to Microsoft Excel files and uploaded to REDCap using automated data entry tools. Paper data will be entered by a single member of the research team with a research coordinator oversight. The research coordinator will track and audit enrollment, attrition, attendance, study and assessment protocol adherence, and online patient-reported outcomes for completion and quality (i.e., range checks for data values) [77], contact participants to address omissions, and maintain all electronic and paper files.

### Analyses {20a, b, c}

Statistical analyses will be performed by an independent statistician and then evaluated and interpreted in a blinded fashion by the author group (results will be written up as two scenarios; group A having had SOAR and group B having had SOAR) prior to breaking the randomization code [78]. To preserve study integrity and mitigate the risk of type 1 errors and premature conclusions, interim analyses are not planned.

Primary analyses will be *intent-to-treat* (by randomization) and missing data will be addressed as outlined below. We will report descriptive statistics for demographic and possible prognostic variables (socioeconomic status, sport participation, time from injury/ACLR, concomitant injury/surgery, rehabilitation, graft type, reinjury, co-interventions) for all participants, those lost to follow-up, and by study group, and consider or control for group differences when interpreting results.

SOAR superiority will be assessed with a generalized linear mixed regression model (GLMM) for the primary outcome (change in KOOS_4_ from baseline to 6 months) adjusted for continuous [153] baseline KOOS_4_ value, BMI [154, 155], time since ACLR [29], and sex. Given there is a single primary outcome, multiple comparison adjustment is not required. SOAR superiority for secondary outcomes will be assessed with mixed-effect logistic (OA lesion worsening) or linear (individual KOOS subscale scores, KOOS PASS and PIH scores) regression models adjusted for the same variables as the primary GLMM, at stated time points. To gauge the robustness of chosen PASS cut-off scores, we will perform two sensitivity analyses. First, we will consider a cut-point based on the upper bound of the PASS values 95%CI and secondly, a cut-point that would result in 10% more participants in the SOAR group achieving a PASS than the control group; a percentage agreed upon by our clinician partners as sufficient to change their management approach for this patient population considering patients SES, program costs, and the possibility of adverse events.

A strength of GLMMs is that they use all available data by including variables with missing outcome values. The relationship shape between continuous covariates and outcome change will be assessed prior to analyses. Nonlinearities will be addressed via fractional polynomial or restricted cubic spline transformations, as indicated.

Robust statistical methods will be used to address missing data and minimize the potential for skewing results by missing data handling. GLMMs produce valid inference under the missing at random (MAR) assumption (a standard assumption and more plausible than missing completely at random). Missing values are MAR when they can be predicted from observed data (demographic/prognostic variables, outcome values). As recommended, significant demographic/prognostic and outcome variables will be included as model covariates [156]. To reduce bias and minimize statistical power loss, we will use likelihood-based direct estimation to handle missing outcome values (equivalent to imputing missing values infinite times) [157]. We will assess the robustness of estimates to MAR assumption violations with the Index of Sensitivity to Nonignorable missingness (ISNI) using the R package “isni” [158–161]). The ISNI employs selection models for non-random missing data and performs sensitivity analyses to measure any attrition bias arising from uneven study arm follow-up rates. If the missingness in demographic/prognostic variables used in the outcome models is > 5% (reducing proposed GLMM sample size), we will use a distribution-free multiple imputation method [162]. The multiple imputation method imposes no distributional assumptions on missing values, avoids implausible or out-of-range imputed values, and can handle arbitrary missing data patterns. We will examine the missingness profile and imputed values to ensure no multiple imputation bias [163, 164].

To explore the effect of gender identity (woman, man, gender-diverse) and sex (female, male, intersex), all outcomes will be described by treatment group stratified by sex or gender as appropriate, at all time points. Stratified analyses will estimate primary and secondary regression models to explore intervention effect estimates by sex (female, male) or gender (woman, man) to inform future studies. Descriptive statistics will explore differences by cis and diverse gender.

The percentage of physiotherapists achieving 85% or more on the fidelity checklist and checklist items with 70% fidelity or more will be reported. Interview recordings will be transcribed and de-identified. Using a constant comparative approach [118] data will be coded and categories developed by comparing and identifying meaningful patterns across codes. High-order themes will elucidate the relationship between categories. We will look for uniqueness by gender and if found, reanalyse the data with a gender lens. Analysis trustworthiness and credibility will be fostered through data immersion, memoing, reflexive journaling and team discussions. An audit of analytic decisions will be kept [165].

Incremental cost utility ratio will be estimated as $${\mathrm{Cost}}_{\mathrm{SOAR}}-{\mathrm{Cost}}_{\mathrm{CONTROL}}/{\triangle\mathrm{QALY}}_{\mathrm{SOAR}}-{\triangle\mathrm{QALY}}_{\mathrm{CONTROL}}$$ for the intervention and post-intervention period.

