### Objectives {7}

The aim of this randomized controlled trial (RCT) is to assess the effectiveness, implementation, and efficiency [56] of a digital 6-month education and exercise therapy program (SOAR) versus a minimal intervention control for people aged 16–35 years at risk of early-onset knee OA due to a first-time ACLR. The primary objective is to assess the average effectiveness of the SOAR program on an aggregate outcome of self-reported knee pain, symptoms, function, and quality-of-life (mean score of the Knee injury and OA Outcome score, pain, other symptoms, function in sport and recreation and quality-of-life subscales; KOOS_4_) [57, 58] of people at risk of early-onset post-traumatic knee OA compared to a minimal intervention at 6 months, with additional follow-up at 12 and 24 months. We hypothesize that, on average, the SOAR program will produce greater improvements in knee-related pain, symptoms, function, and QOL after 6 months (primary end point) and long-term (12- and 24-month secondary endpoints) compared to the minimal intervention control group. Secondary effectiveness (6-, 12- and 24-month between-group difference in change and patient acceptable symptom states (PASS) for symptoms, function and QOL; change in perceived self-management; and 12- and 24-month change in MRI features of knee OA [59] and early cartilage degradation [60]), implementation (provider and participant perceived barriers and facilitators for SOAR delivery) and efficiency (incremental cost-utility ratio [61]) outcomes will also be assessed. Finally, we will explore the effect of the SOAR program on 6-, 12-, and 24-month changes in patient-specific function, knee-related self-efficacy, fear of movement and re-injury, knee extensor and flexor muscle strength, physical activity, adiposity, health-related QOL, and cartilage composition (MRI T2 mapping), and describe features of physiotherapist counseling that promote self-management, program delivery costs, and healthcare resource use.

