### Sample size {14}

The study sample size is based on a primary analysis of superiority of the 6-month KOOS_4_ response to the SOAR program considering pilot RCT data [54], systematic review of meaningful KOOS_4_ thresholds in the study population [42] and typical ACLR and knee OA exercise programs effect sizes (0.45–0.50) [40, 74]. Using a KOOS_4_ response standard deviation of 21 points (pilot RCT), α = 0.05 and 1 − ß = 90%, 66 people/group (regression model with 4 covariates and combined *r*^2^ = 0.3) are needed to detect a mean between group KOOS_4_ minimal important difference (10 points) [42], which is consistent with a 0.476 effect size. A sample of 166 (83/group) allows for 20% attrition. Calculations were done with the analysis of covariance procedure in Power Analysis and Sample Size 13 (NCSS, USA) [75].

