#### Secondary outcomes

##### Knee-related pain, symptoms, function in sport and recreation and QOL

To help interpret the clinical relevance of the KOOS_4_, individual sub-scale scores and the percentage of participants exceeding sub-scale PASS [113] scores (pain 89; symptoms 83; ADL 95, sport 72; QoL 73) [38] will be reported by group and timepoint.

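### The single-primary reason for waiving multiplicity adjustment covers KOOS4 at 6 months only; it does not support the superiority assessments the plan then extends to secondary outcomes

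*Protocol article*

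**What the plan says.** Analyses {20a, b, c} describes the primary model for KOOS4 change to 6 months and continues: "Given there is a single primary outcome, multiple comparison adjustment is not required. SOAR superiority for secondary outcomes will be assessed with mixed-effect logistic" models for OA lesion worsening and linear models for the KOOS subscales, KOOS PASS and PIH, at the stated time points.

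Objectives {7} states a directional hypothesis of greater improvement "after 6 months (primary end point) and long-term (12- and 24-month secondary endpoints) compared to the minimal intervention control group". The same section lists "Secondary effectiveness (6-, 12- and 24-month between-group difference in change and patient acceptable symptom states (PASS) for symptoms, function and QOL", followed by perceived self-management (PIH) and MRI features at 12 and 24 months.

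Under the secondary outcomes, the KOOS paragraph says that "individual sub-scale scores and the percentage of participants exceeding sub-scale PASS [113] scores (pain 89; symptoms 83; ADL 95, sport 72; QoL 73") will be reported by group and time point. It opens by giving these measures the purpose of helping to interpret KOOS4.

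The only significance level in the article is in Sample size {14}: "α = 0.05 and 1 − ß = 90%, 66 people/group". Outcomes are ranked primary, secondary and exploratory. The models by sex and gender are framed as exploratory.

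**The concern.** The two adjoining sentences do different work. The first gives a reason that applies to one test. The second uses the same inferential term, superiority, for a set of other tests and sets no condition on them. A reader following the text could declare SOAR superior on a later KOOS4 visit, on PIH or on MRI worsening at an unadjusted 0.05, whether or not the 6-month primary succeeds.

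What is at stake is the trial's conclusion after a negative or borderline primary. The 12- and 24-month KOOS4 effects matter most here, because they are part of the stated hypothesis and bear directly on a programme meant to protect knee health in the long term. The same section names type I error as a reason for planning no interim analyses, so the authors regard the error rate as something to protect.

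**Working it through.** **1. The plan's own figure, and the per-test level.** The inputs are all from Sample size {14}: "Using a KOOS_4_ response standard deviation of 21 points (pilot RCT"), difference 10 points, "regression model with 4 covariates and combined" r² of 0.3, alpha 0.05 and power 90%.

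- Effect size: 10/21 = 0.476, which matches "which is consistent with a 0.476 effect size".
- Residual SD: 21 × √(1 − 0.3) = 17.57.
- With 66 per group: SE = 17.57 × √(2/66) = 3.059; noncentrality = 10/3.059 = 3.270; df = 132 − 2 − 4 = 126. Two-sided power from the noncentral t is 0.9005.
- With 65 per group, power is 0.896. So 66 per group is reproduced, and 66/0.8 rounds up to 83 per group, 166 in all.
- A one-sided 0.05 would need only 54 per group. The article does not state the sidedness, so I take each test as two-sided 0.05, which is 0.025 in SOAR's favour.

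**2. Counting the secondary contrasts.**

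| Outcome | Contrasts |
|---|---|
| KOOS4 at 12 and 24 months | 2 |
| Five KOOS subscales × 3 visits | 15 |
| Five subscale PASS rates × 3 visits | 15 |
| PIH × 3 visits | 3 |
| MRI worsening × 2 visits | 2 |
| Total | 37 |

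Dropping ADL removes 6 and gives 31. Testing four PIH subscales (+9) and the four example MRI features (+6) gives 52. Setting aside the 30 subscale and PASS contrasts, which have a stated interpretive role, leaves 2 + 3 + 2 = 7.

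**3. Chance of at least one false result when all k nulls are true.** The article gives no correlations, so I assume an exchangeable normal model with correlation ρ. With c = 1.96 and Z standard normal:

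- in SOAR's favour: 1 − E[Φ((c − √ρ Z)/√(1 − ρ))^k]
- in either direction: the same, with Φ(·) replaced by Φ((c − √ρ Z)/√(1 − ρ)) − Φ((−c − √ρ Z)/√(1 − ρ))

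| k | Direction | ρ = 0.3 | 0.5 | 0.7 | 0.9 |
|---|---|---|---|---|---|
| 37 | favouring SOAR | 0.39 | 0.28 | 0.18 | 0.09 |
| 37 | either | 0.72 | 0.55 | 0.37 | 0.18 |
| 7 | favouring SOAR | 0.137 | 0.115 | 0.089 | 0.057 |
| 7 | either | 0.27 | 0.23 | 0.18 | 0.11 |
| 2 (KOOS4 at 12, 24 months) | favouring SOAR | 0.048 | 0.045 | 0.042 | 0.035 |

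The nominal rates for one test are 0.025 in SOAR's favour and 0.05 in either direction. For the other counts at ρ = 0.5, the SOAR-favouring figure is 0.26 (k = 31) and 0.32 (k = 52).

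**4. A less uniform correlation pattern.** A simulation of the 37 contrasts let the assumed correlations differ between subscales, visits, PASS rates, PIH and MRI. It gave 0.27 to 0.41 in SOAR's favour.

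**5. Independence as a bound.** For k = 37 the SOAR-favouring figure is 1 − 0.975^37 = 0.61. These outcomes are clearly not independent: four subscales make up KOOS4, PASS rates dichotomise the subscales, and visits repeat on the same people.

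**The case against.** The strongest reply has four parts.

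- **The waiver is correct where it stands.** One primary outcome at one time point needs no adjustment. This is true, and the primary error rate is 0.05 with or without any change.
- **The secondaries are already ranked below the primary, and most have a supportive role.** The article has three tiers, and it presents the subscales and PASS rates as aids to reading KOOS4. This stands for 30 of the 37 contrasts and is why the seven-contrast figures matter. It does not settle the point, because the superiority sentence names subscales and PASS along with PIH and lesion worsening, and KOOS4 at 12 and 24 months carries its own directional hypothesis.
- **A testing order within the secondaries belongs in the SAP, which is not shown.** I agree that its absence here is no fault. The point rests on what the article does state: a reason that covers one test, followed directly by superiority wording for others.
- **Unadjusted secondaries are common, and two interpretations are to be written before unblinding.** Unadjusted results are acceptable when read as supportive, but the article does not restrict them to that reading. Writing interpretations blind limits selective claims; it does not lower the error rate.

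A reader might infer that a false superiority claim on some secondary is likely. The figures do not support that. The values above one half come from counting errors in favour of control as well, or from near-independence, and all assume that every null is true. Nor does the article say that a trial conclusion will rest on a single secondary.

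**Conclusion.** The concern holds in limited form, as a cheap improvement. The primary analysis is sound and its type I error is unaffected. The fault is that the waiver's reason is narrower than the inference following it, and nothing shown ties later or secondary superiority claims to a positive 6-month result.

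For the seven contrasts outside the subscale and PASS set, the SOAR-favouring error is roughly 2 to 5 times the nominal 0.025 (0.057/0.025 = 2.3; 0.137/0.025 = 5.5). Over all 37 it is roughly 4 to 16 times (0.09/0.025 = 3.6; 0.39/0.025 = 15.6). For KOOS4 at 12 and 24 months alone the inflation is modest, at most about twice nominal (0.048/0.025 = 1.9).

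These sizes rest on a global null, two-sided 0.05 per test, assumed correlations of 0.3 to 0.9 and the count above. The direction of the conclusion does not depend on the exact count or correlation. It would be wrong to say that the plan has no hierarchy of outcomes; what the text shown lacks is a gate on the primary and a limit on what may be claimed.

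**What to change.** Three changes in Analyses {20a, b, c}, with a matching registry note:

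1. Limit the waiver to the primary, for example: *The single primary test is KOOS4 change at 6 months, two-sided 0.05; no adjustment is needed for this test.*
2. Replace the superiority wording for the secondaries, for example: *Between-group differences in secondary outcomes will be estimated and reported as supportive, with unadjusted 95% confidence intervals; no claim of superiority will be based on them.*
3. If confirmatory claims are wanted for KOOS4 at 12 and 24 months, exempt these two from item 2 and add: *If the 6-month test is significant, KOOS4 at 12 months and then at 24 months will be tested in that order, each at two-sided 0.05, stopping at the first non-significant result.* This holds the error over the three KOOS4 tests at 0.05.

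The cost is a paragraph of text. The 166 participants, the data collected, the primary test and its power stay as they are. The price is that after a negative 6-month result no later or secondary finding can be called superiority. The change should be made before the data are unblinded.

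### The second PASS sensitivity analysis defines its cut-point by a 10% advantage for SOAR, so the difference found there cannot show whether the result at the published PASS values is robust

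*Protocol article*

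**What the plan says.** The secondary outcomes section fixes the PASS values for the five KOOS subscales in advance: "pain 89; symptoms 83; ADL 95, sport 72; QoL 73". The share of participants above each value is reported by group and time point, to help readers interpret the KOOS4 result.

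The Analyses section then states: "To gauge the robustness of chosen PASS cut-off scores, we will perform two sensitivity analyses". The first uses "a cut-point based on the upper bound of the PASS values 95%CI". The second uses "a cut-point that would result in 10% more participants in the SOAR group achieving a PASS than the control group". The 10% is explained as "a percentage agreed upon by our clinician partners as sufficient to change their management approach".

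The same section plans blinded interpretation, in which "results will be written up as two scenarios; group A having had SOAR and group B having had SOAR" before the code is broken. The section on blinding and bias says the same.

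The article does not say how the result at the second cut-point will be used, or what happens if no cut-point, or more than one, gives 10%.

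**The concern.** A sensitivity analysis of a threshold should change the threshold for a reason unrelated to the treatment comparison and then see whether the comparison changes. The first analysis does this. The second reverses it: the size of the comparison is chosen and the threshold is whatever produces it. An estimate that was the selection criterion cannot also be evidence.

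The 10% is a benchmark for judging an observed difference, because the clinician partners named it as enough to change their management. Used to choose the threshold, it no longer judges anything. A reader of the trial report may then see a cut-point at which SOAR meets the clinicians' criterion and take it as support, although such a cut-point can turn up when SOAR has no effect.

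The rule also favours a named arm, so applying it requires knowing, or assuming, which group is SOAR.

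**Working it through.** **1. The plan's own figures.** The only design calculation is for the primary outcome. Its inputs, from the sample size section, are an SD of 21, a difference of 10 points, α of 0.05, 90% power, four covariates with r² of 0.3, and attrition of 20%. The stated result is 66 per group, raised to 83.
- Residual SD = 21 × √(1 − 0.3) = 17.57.
- The two-sided normal approximation gives 65 per group. With the noncentral t and 4 covariates, power is 0.896 at 65 and 0.9005 at 66.
- 66 / 0.8 = 82.5, so 83 per group and 166 in total.

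These figures reproduce. None was made for the PASS analysis. The sizes 66 (after attrition) and 83 (as randomised) are used below. The 10% is read as 10 percentage points.

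**2. The difference at the chosen cut-point.** Proportions move in steps of 1/n. The step nearest 10% is 7/66 = 10.6% or 8/83 = 9.6%. A simulation took the cut-point whose observed difference was closest to 10 points, whenever some cut-point reached 10 (4,000 trials per setting; assumed normal scores limited to 0-100, control mean 75, 1-point grid). For SDs of 15, 18 and 21 and true shifts from −5 to +10 points, the mean chosen difference stayed within 0.097-0.106, with SD at most 0.006. A fixed cut-point does respond. At 73 (the QoL PASS), SD 18 and 66 per group:

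| True shift (points) | Mean difference at fixed cut 73 | Mean difference at derived cut |
|---|---|---|
| −5 | −10.9% | 10.5% |
| 0 | 0.1% | 10.5% |
| +5 | 10.8% | 10.6% |
| +10 | 20.2% | 10.5% |

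**3. How often a qualifying cut-point exists with no true effect.** Quantity: P(max over cut-points of [SOAR − control proportion] ≥ 0.10). Assumed mean 70, SD 18, 20,000 trials per setting. Repeat runs differ by about one percentage point.

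| Score levels | 66 per group | 83 per group |
|---|---|---|
| 69 | 0.42 | 0.32 |
| 37 | 0.38 | 0.28 |
| 21 | 0.34 | 0.25 |
| 17 | 0.31-0.32 | 0.23 |

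No cut-point qualifies in the rest: 58-69% at 66 per group and 68-77% at 83. With mean 75, SD 15-21 and a 1-point grid, the existence figures are 42-44% and 33-35%. For a continuous score the large-sample value is exp(−2 × (n/2) × 0.10²): exp(−0.66) = 0.517 and exp(−0.83) = 0.436, an upper reference for these discrete scores. If SOAR is truly 2 points worse (21 levels), a qualifying cut-point still exists in about 16% and 10% of trials.

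**4. Uniqueness.** In the simulation of step 2, with a true shift of 5 points, the cut-points giving about 10% typically span 18-21 score points (median). With no shift the median span is 5-11 points.

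**5. What a test there would show.** For a pooled two-proportion test at a difference of exactly 10 points, p depends only on n and on where the cut falls. Example at a control rate of 50% and n = 66: SE = √(2 × 0.55 × 0.45 / 66) = 0.0866, z = 1.155, p = 0.248. Over control rates of 10-80%, p runs from 0.11 to 0.25 at 66 per group and from 0.07 to 0.20 at 83.

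**The case against.** The best defence is that this is a tipping-point analysis. The stated aim concerns the cut-offs, and nothing says superiority will be declared at the derived one. Finding the score at which the clinicians' 10% is reached, and comparing that location with the published PASS value, would be a legitimate description. This partly stands: whether a crossing exists, and where, does carry information. But the article presents the derived value as an alternative PASS cut-point and does not describe this use. Leaving detail to an analysis plan does not help either, because the selection rule itself is what is stated.

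Four stronger readings might be inferred, and the document does not support them:

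- **That the rule picks the place most favourable to SOAR.** It targets 10%, not the maximum. With a true 10-point shift the fixed cut at 73 shows about 20 percentage points, so the rule would move to a place less favourable to SOAR.
- **That it always yields a SOAR advantage.** Under no effect, most simulated trials have no qualifying cut-point.
- **That it breaks the blinding.** The rule can be run with A as SOAR and again with B as SOAR, which fits the planned two-scenario write-up. The article simply does not say so.
- **That 31-42% is a false-positive rate.** It is the chance that a cut-point exists. No test is specified there, and for control rates of 10-80% a test would give p above 0.05.

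**Conclusion.** The concern holds in limited form. Because the cut-point is defined by the between-arm result, the difference at it is about 10 points whatever the true effect, and it cannot support or undermine the conclusion at the published PASS values. This follows from the wording and needs no distributional assumption.

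The existence figures (about 31-42% at 66 per group and 23-32% at 83, per subscale and time point, with no true effect) rest on an assumed mean, SD and number of score levels that the article does not give. Other assumptions move them by several points, up to 44% and 35%, without changing the conclusion.

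The reach is small: one of two sensitivity analyses of a secondary outcome. The main PASS cut-offs are fixed in advance, and the primary KOOS4 analysis and its sample size are untouched. The plan should still be changed, because PASS is there to convey clinical relevance and the 10% is tied to a decision about management.

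**What to change.** Replace the outcome-derived cut-point with cut-points fixed in advance: for each subscale, the published PASS value and the lower and upper bounds of its 95% CI. At each, report the difference in proportions (SOAR minus control) with a 95% CI, and use 10 percentage points as the benchmark against which that difference and its interval are judged.

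If the location of the 10% crossing is of interest, plot both arms' cumulative distributions over all cut-points as a descriptive tipping-point display. State that no test or claim of superiority attaches to it, that there may be no crossing or several, and that it will be produced under both A/B labelings while interpretation is blinded.

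The cost is a change of wording before unblinding, one added analysis at the lower bound, and the loss of the estimate at the derived cut-point, which carried no information about the treatment effect. Sample size and data collection do not change.

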### Allocation {16a, b, c}

After consenting and baseline testing, participants will be randomly assigned to SOAR or control groups in a 1:1 (concealed) allocation ratio, stratified by sex (to enable sex and gender-based analyses) in variable block sizes (to balance group uniformity and reduce sequence predictability). A research coordinator will provide participants with an opaque sealed envelope containing group allocation assigned by a software randomization module (REDCap) [76, 77] with a computer-generated randomized number schedule made by an arms-length statistician. An automated audit trail will track randomization date, stratum, and allocation.

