### Interventions {6b, 11a}

An overview of the experimental and control interventions consistent with the TIDieR guidelines is provided in Table 3. After the baseline assessment, participants will receive their intervention specific workbook (in the sealed opaque envelope containing their group allocation), a wrist-worn activity tracker (Fitbit® Inspire 3, Fitbit Inc, San Francisco, CA, USA) and a resistance loop set (Chimaera®) providing up to 100 lbs of load to enable exercise progression. After agreeing to Fitbit’s® privacy policy, participants will be oriented to the device, instructed to wear it 24 h per day, and share their Fitbit® activity “Dashboard” with researchers. Participants will be asked to refrain from introducing new knee-related treatments (health or fitness provider) beyond the interventions they are assigned. Any co-interventions will be captured with the Health Resource Utilization Questionnaire (HRU; see below).

**Table 3 Tab3:** Overview of interventions according to the TIDieR guideline

Brief name	SOAR program (intervention)	Minimal intervention control (control)
Why	• Evidence-based consensus recommendations to optimize knee health after injury include person-centered education and exercise therapy targeting self-management and risk factors for re-injury and osteoarthritis (muscle weakness, inactivity, adiposity) • Patients identify a “post-ACLR rehabilitation” care gap related to learning how to self-manage their long-term knee health	• Offer evidence-based principles for ACLR rehabilitation and knee health but is inert of tailoring, goal setting, intentional and reflective self-monitoring, or performance feedback • Provide an expectation of therapeutic benefit, and control for natural history, regression to the mean, and contextual effects

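### The covariate rules in the Analyses section conflict and, read literally, could adjust the primary effect for variables that arise after randomisation

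*Protocol article*

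**What the plan says.** All of this is in the protocol article.

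- **Analyses {20a, b, c}, primary model.** The 6-month change in KOOS4 is modelled with adjustment for baseline KOOS4, BMI, time since ACLR and sex. Secondary models use the same set. The primary analysis is described as intention-to-treat.
- **Sample size {14}.** The calculation assumes the same number of covariates: "66 people/group (regression model with 4 covariates and combined" r² of 0.3.
- **Analyses, missing-data text.** After explaining the missing-at-random assumption, the plan states that "significant demographic/prognostic and outcome variables will be included as model covariates".
- **Analyses, descriptive text.** The possible prognostic variables to be described end with "reinjury, co-interventions) for all participants, those lost to follow-up, and by study group, and consider or control for group differences when interpreting results".
- **Interventions {6b, 11a}.** "Any co-interventions will be captured with the Health Resource Utilization Questionnaire". Data collection procedures {11d, 18a, b} adds that this happens monthly throughout the study.

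**The concern.** The first two statements describe a closed model with baseline covariates only. The next two, as written, open it. The missing-data sentence uses mandatory wording and speaks of covariates in the model, not of auxiliary variables for imputation. It does not say what counts as significant, which outcomes are meant, or that values must be from baseline. The descriptive sentence allows control for arm differences in a list that contains at least one post-allocation variable.

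A variable measured after allocation can itself be an effect of allocation. Controls receive one physiotherapist session and SOAR participants receive many, so different uptake of outside care is plausible. Adjusting for such a variable removes whatever part of the effect passes through it. If the variable also shares unmeasured causes with KOOS4, adjustment introduces collider bias. Either way the coefficient for treatment stops being the total effect of assignment, even though everyone is analysed in the arm to which they were randomised. At stake are the meaning of the primary estimate and its comparison with the 10-point minimal important difference.

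**Working it through.** **1. The plan's own figure.** Inputs from Sample size {14} and Allocation {16a, b, c}: "response standard deviation of 21 points (pilot RCT"), difference 10 points, α = 0.05 (taken as two-sided), power 90%, four covariates with r² = 0.3, and "1:1 (concealed) allocation ratio, stratified by sex".

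- Standardised effect: 10/21 = 0.476, as stated ("consistent with a 0.476 effect size").
- Residual SD: 21 × √(1 − 0.3) = 17.57.
- Power from the noncentral t, with noncentrality 10/(17.57 × √(2/n)) and df = 2n − 2 − 4: n = 65 per arm gives 89.6%, and n = 66 gives 90.05%.
- Attrition: 66/(1 − 0.20) = 82.5, rounded up to 83 per arm, or 166 in total, as stated ("A sample of 166 (83/group) allows for 20% attrition").

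The sample size reproduces with exactly four covariates. No stated number is in dispute.

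**2. Which listed variables are post-randomisation?**

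- *Co-interventions:* clearly so. Table 2 requires that participants are not receiving knee care at entry, they are asked not to start new knee treatment, and uptake is logged monthly.
- *Reinjury:* not stated. The term is absent from the baseline characteristics in Outcomes {12}, but prior knee injury is recorded there.
- *Outcome variables:* baseline KOOS4 would qualify, and so would any 6-month outcome. The sentence does not choose between them.

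**3. Illustration of the mechanism.** Simulated trials of 2 × 66, residual SD 17.57, with one baseline covariate carrying r² = 0.3. The structures below are assumptions and do not come from the documents.

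*(a) Adjusting for a follow-up outcome.* Suppose SOAR shifts it by 0.476 of its SD and its residual correlation with KOOS4 is ρ. The adjusted effect is 10 − ρ × 17.57 × 0.476.

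| ρ | Formula | Simulated | Power |
|---|---|---|---|
| 0.3 | 7.5 | 7.5 | 69% |
| 0.5 | 5.8 | 5.8 | 56% |
| 0.7 | 4.1 | 4.2 | 45% |

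Without the added covariate: 10.0 points and 90% power.

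*(b) Adjusting for a co-intervention.* Uptake is 35% in controls and 10% in SOAR for a participant of average unmeasured knee status, and higher with worse status. The co-intervention has no effect of its own on KOOS4. The unmeasured status accounts for 0.5 (moderate) or 0.7 (strong) of the residual SD, with a log-odds slope of 1 or 1.5 on uptake.

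| Sharing | True effect | Unadjusted for it | Adjusted for it | Rejection rate, before and after |
|---|---|---|---|---|
| Moderate | 10 | 10.0 | 8.3 | 90%, 74% |
| Strong | 10 | 10.0 | 6.9 | 90%, 63% |
| Moderate | 0 | 0.0 | −1.8 | 5.0%, 8.7% |
| Strong | 0 | 0.0 | −3.1 | 5.6%, 18.0% |

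*(c) Selecting baseline covariates only.* Eight candidates, three of them prognostic, each entered if p < 0.05 against the outcome: type I error 5.3% without selection and 5.1% with it.

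The distortion in (a) and (b) comes from adjusting for post-randomisation variables. In (c), selection on baseline variables alone produces none of note.

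**The case against.** The strongest defence is that the primary model is already closed. Four covariates are named, the sample size uses four, and the secondary models inherit the same set. The contested sentence sits in the justification for missing at random and may only explain that set: sex, BMI and time since ACLR are demographic or prognostic, and baseline KOOS4 is an outcome variable. The word significant may mean important, since no threshold or selection step is given. The same text later applies the demographic/prognostic label to variables used in the outcome models, which fits this reading. The sentence about arm differences concerns descriptive statistics and ends with interpretation of results. Analysts work with masked group labels, and an unseen statistical analysis plan may settle the matter.

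Much of this stands. A reader might infer that the primary effect is certain to be conditioned on post-randomisation variables. The text supports only that it could be. A reader might also take reinjury to be a post-randomisation variable, but its timing is not given. Nor does choosing baseline covariates by significance inflate type I error, on the check above. It leaves the model unfixed, which is a lesser fault.

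What does not stand is that nothing needs correcting. The benign reading requires a limit to baseline that the sentence does not contain. This is not detail left for an analysis plan, because the article states two covariate rules that disagree. Masked labels do not prevent bias from a mediator or collider, which arises whatever the arms are called.

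**Conclusion.** The concern holds as a badly fixed rule. The article specifies a four-covariate baseline model and then, in the same section, uses wording under which further variables could enter, including co-interventions recorded after allocation. If applied that way, the primary estimate would no longer be the intention-to-treat effect.

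The size cannot be derived from the documents. The results of about 8.3 to 4.2 points against a true 10 rest on assumed uptake, correlation and unmeasured causes. They should not be read as an expected error, or as showing that the bias always runs towards zero: adjusting for a co-intervention that itself helps, and that controls take more often, would push the other way. Nor do the documents support discarding the planned likelihood-based handling of missing outcomes. Replacing it outright with multiple imputation would be a preference of method.

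**What to change.** Three changes of wording in Analyses {20a, b, c}:

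1. In the missing-data text, replace the contested sentence with a statement that the primary and secondary outcome models contain treatment and the pre-named baseline covariates only, with no selection by significance or by observed imbalance between arms.
2. In the descriptive text, state that co-interventions and any post-randomisation reinjury are reported by arm and are not adjusted for in the primary model. Say also what reinjury covers in time.
3. Keep likelihood-based estimation for missing outcomes. If post-baseline predictors of missingness are wanted, use them only as auxiliary variables in a named sensitivity analysis, for example multiple imputation.

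The sample size is unaffected: four covariates still give 66 analysed per arm and 166 randomised. No data collection changes. The cost is the amendment of the text and, if the third item is taken up, one extra analysis. Trial status estimates completion in December 2028, which leaves time to settle this before unblinding.
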